## Abstract

**Background:**

Excessive weight gain during pregnancy is associated with complications for both the mother and her infant including gestational diabetes, hypertensive disorders, operative delivery, and long-term obesity. A healthy diet during pregnancy promotes healthy gestational weight gain and determines fetal epigenetic programming in infants that impacts risk for future chronic disease.

**Objective:**

This project will examine the impact of grocery delivery during pregnancy on the weight, diet, and health outcomes of young pregnant women and their infants.

**Methods:**

A three-arm randomized controlled trial design will be performed. A total of 855 young pregnant women, aged 14-24 years, from across the state of Michigan will be enrolled and randomized equally into the three study arms. Participants in arm one (control) will receive usual care from the Special Supplemental Nutrition Program for Women, Infants, and Children (WIC); arm two will receive WIC plus biweekly grocery delivery; and arm three will receive WIC plus biweekly grocery and unsweetened beverage delivery. Weight will be assessed weekly during pregnancy, and total pregnancy weight gain will be categorized as above, below, or within guidelines. Additionally, dietary intake will be assessed at three time points (baseline, second trimester, and third trimester), and pregnancy outcomes will be extracted from medical records. The appropriateness of pregnancy weight gain, diet quality, and occurrence of poor outcomes will be compared between groups using standard practices for multinomial regression and confounder adjustment.

**Results:**

This study was funded in April 2021, data collection started in December 2021, and data collection is expected to be concluded in 2026.

**Conclusions:**

This study will test whether grocery delivery of healthy foods improves weight, diet, and pregnancy outcomes of young moms with low income. The findings will inform policies and practices that promote a healthy diet during pregnancy, which has multigenerational impacts on health.

**Trial Registration:**

ClinicalTrials.gov NCT05000645; https://clinicaltrials.gov/ct2/show/NCT05000645

**International Registered Report Identifier (IRRID):**

DERR1-10.2196/40568

## Introduction

The United States has one of the highest adolescent pregnancy rates among high-income countries with almost 800,000 15- to 24-year-old women giving birth in 2021 [1-3]. Among youth who give birth, over half gain excessive weight during pregnancy [4-8]. Excessive weight gain during pregnancy is associated with complications for both the mother and her infant including gestational diabetes, hypertensive disorders, operative delivery, and long-term obesity [5,9-15]. Young women with low income and those from racial/ethnic minority groups have the highest rates of adolescent pregnancy and face significant barriers to healthy food and beverage consumption and physical activity during pregnancy [16-21].

A healthy diet during pregnancy promotes healthy weight gain among mothers [22] and impacts permanent fetal epigenetic programming that determines future risk for chronic disease among infants [23,24]. However, most youth consume suboptimal diets that can lead to unhealthy weight gain in pregnancy [25-28]. Sugar-sweetened beverage (SSB) consumption during pregnancy is further associated with lower diet quality and greater total energy intake among pregnant women [29].

Grocery delivery is a well-established and inexpensive service that removes logistical barriers to obtaining healthy foods and beverages. There are numerous grocery delivery services (eg, Shipt.com, Instacart, FreshDirect, Amazon Fresh, Peapod, and Google Express) that help make obtaining fresh food and groceries more convenient for those who cannot or do not shop in person. However, grocery delivery is predominantly used by affluent middle-aged women [30,31], and few efforts have yet explored online grocery ordering and delivery for young pregnant Special Supplemental Nutrition Program for Women, Infants, and Children (WIC) beneficiaries [32], a population with significant logistical barriers to obtaining healthy foods.

To address this critical problem, we developed Special Delivery, a program that uses grocery delivery to overcome these logistical barriers to a healthy diet during pregnancy among pregnant young women with low income to prevent excessive gestational weight gain.

The aim of this randomized controlled trial is to assess whether grocery delivery of healthy foods to the homes of young women during pregnancy will promote healthy pregnancy weight gain. The study will also assess secondary outcomes of diet quality, pregnancy complications, and delivery outcomes. Our long-term goal is to identify effective interventions to support a healthy diet during pregnancy and promote healthy weight gain among pregnant young women with low income.

The primary hypotheses to be tested are that the home delivery of healthy foods will promote healthy weight gain during pregnancy and that the addition of unsweetened beverage delivery will promote more healthy weight gain. The findings will inform policies and practices that promote a healthy diet during pregnancy, which may have multigenerational impacts.

## Methods

### Study Design

This study is a three-arm randomized controlled trial with an additive parallel design. Enrollment in the study is rolling and starts as early as possible in the pregnancy (by 21 weeks’ gestation). The intervention period begins at enrollment and continues to the end of pregnancy/birth (Figure 1). Data collection occurs throughout the study with surveys at baseline, the second trimester, the third trimester, and after delivery, as well as short weekly assessments. Upon enrollment in the study, participants will be randomized to one of three groups: usual WIC (arm 1; control), usual WIC + delivery of WIC-approved food (arm 2), and usual WIC + delivery of WIC-approved food plus unsweetened beverages (arm 3).

**Figure 1 figure1:**
[figure not shown]
Participant study timeline. WIC: Special Supplemental Nutrition Program for Women, Infants, and Children.

Specifically, we will be testing the following hypotheses:

Mothers who receive free grocery delivery of WIC-approved healthy foods will have healthier weight gain during pregnancy, higher-quality diets, and fewer perinatal complications than peers with usual WIC benefitsMothers who receive free grocery delivery of WIC-approved healthy foods plus unsweetened beverages will have healthier weight gain during pregnancy, higher-quality diets, and fewer perinatal complications than peers with usual WIC benefits and home delivery of WIC-approved foods only

The rationale for the study is that grocery delivery will address barriers to accessing healthy foods and will therefore facilitate a healthier diet and prevent excessive weight gain during pregnancy.

### Ethics Approval

This study was approved by the University of Michigan Institutional Review Board (HUM00190614).

### Participants

The study will include 855 young moms who are pregnant with their first child. Those with previous births are excluded to limit the impact of variable past pregnancy experiences and habits on the intervention. Participants will be included from across the state of Michigan based on the criteria below.

Inclusion criteriaYouth (ages 14-24 years)Enrolled in WICGestational age ≤20 weeksSMS text message capabilityHealthy singleton pregnancyNulliparousConsume SSBsLiving within delivery zone of a grocery delivery serviceExclusion criteriaNon-English speakingParticipants who live at the same addressHigh-risk pregnancy requiring specialized care

### Procedure

Participants in this study will be referred from WIC offices, online study recruitment sites, or other clinical and community organizations that serve young pregnant women across the state of Michigan. Interested women complete an online screening and enrollment survey or call the study line for assistance in completing the survey. Consent is obtained verbally or in completion of the online enrollment form and a copy of the consent form is emailed to participants.

### Sample Size Determination

Based on nationally representative studies of weight gain in pregnancy [4], we anticipate 30%, 45%, and 60% of participants in arm 1 (control), arm 2 (WIC + food delivery), and arm 3 (WIC + food plus unsweetened beverage delivery), respectively, to gain weight within the Institute of Medicine guidelines [5,33]. The sample size was determined using methods for comparing independent proportions, and a conservative alpha value of .01 was set for significance to address the multiple testing of 3 comparisons. A sample size of 774 (258 per arm) after attrition will have over 80% power (2-tailed) to detect these differences as statistically significant. Accounting for an anticipated 10% attrition rate based on our preliminary study and low-burden design, we will aim to recruit 285 participants per study arm (855 total).

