### Randomization

Upon completion of baseline screening and assessments, 855 pregnant young women will be randomly assigned to either the control group or one of the two experimental groups. We will use county-level block randomization to assign participants in a 1:1:1 ratio to the three study arms. The treatment assignments will be created and stored in the Consulting for Statistics, Computing and Analytics Research randomization tool managed by the University of Michigan. No treatment assignments will be made until after collection of baseline data (consent, demographic survey, diet recalls, and other baseline questionnaires). At this time, the participant will be notified of their arm assignment and additional details required for grocery delivery (delivery address, day, and time) will be collected from participants in arms 2 and 3. All personnel who assess study outcomes are masked to group assignment. Participants and staff implementing the grocery delivery are not masked to group assignment.

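### A Holm step-down at the same 3% familywise bound would give more power than the fixed .01 per comparison; an optional gain, not an error

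*Protocol article*

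**What the plan says.** All of the multiplicity text is in the protocol article under Sample Size Determination.

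- Assumed rates of weight gain within guidelines: "we anticipate 30%, 45%, and 60% of participants in arm 1 (control), arm 2 (WIC + food delivery), and arm 3" respectively.
- Method: "The sample size was determined using methods for comparing independent proportions".
- Multiplicity: "a conservative alpha value of .01 was set for significance to address the multiple testing of 3 comparisons".
- Size: 258 per arm (774) after attrition, which "will have over 80% power (2-tailed) to detect these differences as statistically significant". Recruitment is 285 per arm (855).

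The hypotheses listed under Study Design set arm 2 against usual WIC. They also set arm 3 against both other arms: it should do better "than peers with usual WIC benefits and home delivery of WIC-approved foods only". Data Analysis specifies an adjusted multinomial logistic regression across arms and gives no further multiplicity rule. No familywise level is stated anywhere, and no step-down, hierarchical or closed procedure is named.

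**The concern.** A single-step rule holds every comparison at .01 even after another has been clearly rejected. Under the plan's own rates, arm 1 vs arm 3 (30% vs 60%) is almost certain to be rejected, after which the other two pairs no longer need so strict a level to keep the same familywise bound.

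The pairs that lose power are the two adjacent steps, arm 2 over arm 1 and arm 3 over arm 2. These carry the two primary hypotheses: that food delivery helps, and that adding unsweetened beverages helps further. What is at stake is power that could be had from the same 855 participants.

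**Working it through.** **Inputs.** From Sample Size Determination: rates .30/.45/.60, 258 analysed per arm, two-sided alpha .01, three comparisons. From Randomization: 1:1:1 allocation. The three comparisons are read as the pairs 1 vs 2, 2 vs 3 and 1 vs 3.

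**Step 1: reproduce the plan's figure.** Two independent proportions, pooled variance under the null, no continuity correction, with p̄ the mean of the two rates:

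n = [z(.995)·√(2p̄(1−p̄)) + z(.80)·√(p₁q₁+p₂q₂)]² / (p₁−p₂)²

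- 45% vs 60%: √(2 × .525 × .475) = .7062 and √(.2475 + .24) = .6982. (2.5758 × .7062 + .8416 × .6982)² / .0225 = 257.4, so **258**, the stated size.
- 30% vs 45%: √(2 × .375 × .625) = .6847 and √(.21 + .2475) = .6764. The same formula gives 241.9, so 242.

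The match at 258 shows that .01 was applied to each comparison.

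**Step 2: power per comparison at 258 per arm.** Power = Φ{[√n·|p₁−p₂| − z·√(2p̄q̄)] / √(p₁q₁+p₂q₂)}, with q̄ = 1−p̄.

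- 1 vs 2: (2.409 − 1.764)/.6764 = .955, so 83.0%.
- 2 vs 3: (2.409 − 1.819)/.6982 = .845, so 80.1%.
- 1 vs 3: above 99.9%.

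The stated power above 80% is therefore right for each comparison.

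**Step 3: the error bound.** Three tests at .01 give at most 3 × .01 = .03. Holm at total .03 compares the smallest p-value with .03/3 = .01, the next with .03/2 = .015 and the last with .03, stopping at the first failure. Any set of p-values at or below .01 passes these steps too, so Holm rejects everything the fixed rule rejects. It needs no independence or ordering assumption.

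**Step 4: why the gain is large at the planned rates.** Once 1 vs 3 is rejected, the adjacent pairs face .015 and .03. The Step 2 formula at .03 gives 91.4% (1 vs 2) and 89.5% (2 vs 3).

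**Step 5: simulation.** Three independent binomial arms of 258, unadjusted pooled z tests, two-sided, 1,000,000 trials:

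| True rates | Quantity | Fixed .01 | Holm .03 |
|---|---|---|---|
| 30/45/60% | 1 vs 2 | 83.0% | 91.3% |
| | 2 vs 3 | 79.5% | 89.6% |
| | both adjacent steps | 63.2% | 81.2% |
| 30/40/50% | 1 vs 2 | 42% | 53% |
| | 2 vs 3 | 38% | 49% |
| | both adjacent steps | 8% | 23% |
| 30/45/45% | 1 vs 2 | 83% | 86% |

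The simulated 79.5% for 2 vs 3 and the 80.1% by formula differ only through the normal approximation; this is not a shortfall in the plan. In the first two scenarios, the chance that all three pairs are significant equals the chance for both adjacent steps.

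**Step 6: false positives.**

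| True rates | False rejection | Fixed .01 | Holm .03 |
|---|---|---|---|
| 30/30/30% | any pair | 2.6% | 2.6% |
| 30/45/45% | 2 vs 3 | 1.0% | 2.2% |
| 30/30/45% | 1 vs 2 | 1.0% | 2.2% |
| 30/30/60% | 1 vs 2 | 1.0% | 3.0% |

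All stay within the .03 bound, but with one truly equal pair the actual rate is two to three times higher under Holm.

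**The case against.** **The plan is valid as written.** This stands. The size reproduces, the power is right per comparison, and .01 controls the familywise error. A reader might infer from the 63% that the trial is underpowered or that its power statement is false. The documents do not support that: the statement is per comparison, the hypotheses can each be reported alone, and nothing makes success depend on all differences being significant. The 63% and 81% describe how often both primary hypotheses would be supported together, not a target that the plan set.

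**The gain is not free.** This also stands. The bound is unchanged, but the error rate for a single true null rises from about 1% to 2–3%. The article states .01 and never .03, so a team that wants every claim held at .01 has made a coherent choice. A total of .05 would give still more power, but it changes the error level and is a separate trade-off.

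**The full analysis plan may already step down.** Possible, since it is not shown. The published sentence, however, gives .01 as the significance level for the comparisons.

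**Holm is one option among several.** True. For three pairwise comparisons, Shaffer's step-down (.01/.03/.03) rejects slightly more: 81.3% against 81.2% for both adjacent steps at the planned rates. Holm is suggested for its simplicity.

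**The figures use unadjusted tests.** The planned analysis is an adjusted three-category regression, so the power figures are indicative only. The ordering of the two rules does not depend on the test used.

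**Conclusion.** The point holds as an efficiency gain. At the familywise bound that three .01 tests imply, Holm never rejects less than the fixed rule. At the planned rates it adds about 8 points of power for arm 1 vs 2, 10 points for arm 2 vs 3, and 18 points for both together. With smaller steps (30/40/50%) it adds about 11, 11 and 15 points; if beverages add nothing, about 3 points for arm 1 vs 2.

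This rests on two readings: that the three comparisons are the three pairs of arms, and that the sizing alpha is also the decision rule, which the words on significance support. It is a cheap, optional improvement.

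**What to change.** Before outcomes are compared by arm, replace the fixed-level rule with a sentence to this effect: the three pairwise arm comparisons of the primary outcome are tested by Holm's step-down procedure at a total two-sided alpha of .03 (.01, .015, .03). Keep 258 analysed and 285 recruited per arm. If the full analysis plan already contains a step-down rule, bring the published sentence into line with it.

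The cost is one sentence, the higher false-positive rate for a single truly equal pair shown above, and confidence intervals that no longer correspond simply to the test. Intervals at 99% can still be reported beside the Holm decisions. If the team prefers to hold each claim at .01, the present rule can stand, with that intention stated.

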### Randomization

Upon completion of baseline screening and assessments, 855 pregnant young women will be randomly assigned to either the control group or one of the two experimental groups. We will use county-level block randomization to assign participants in a 1:1:1 ratio to the three study arms. The treatment assignments will be created and stored in the Consulting for Statistics, Computing and Analytics Research randomization tool managed by the University of Michigan. No treatment assignments will be made until after collection of baseline data (consent, demographic survey, diet recalls, and other baseline questionnaires). At this time, the participant will be notified of their arm assignment and additional details required for grocery delivery (delivery address, day, and time) will be collected from participants in arms 2 and 3. All personnel who assess study outcomes are masked to group assignment. Participants and staff implementing the grocery delivery are not masked to group assignment.

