**Confounders/modifiers**					
	Age, race, ethnicity, socioeconomic status, home environment, food insecurity	Demographic survey		At enrollment	
	Physical activity	Physical activity survey		Weekly during pregnancy	
	Food behaviors	Cooking frequency, fast-food frequency, cooking confidence, eating disorder examination		At enrollment, postpartum	
	Body shape preference	Pulvers body image instrument		At enrollment, postpartum	
	WIC nutrition visits and food benefits redeemed	WIC record review		Postpartum	

^a^ASA24: Automated Self-Administered 24-hour.

^b^WIC: Special Supplemental Nutrition Program for Women, Infants, and Children.

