### Data Analysis

To understand the effect of grocery delivery on pregnancy weight gain, diet quality, and health outcomes, weight will be measured weekly, dietary quality will be assessed twice per trimester, and perinatal outcomes will be assessed at the end of the pregnancy. All analyses will follow the intention-to-treat principle. Prior to analysis, assessment of missing data will be completed and appropriately imputed using multiple imputation methods [65].

Our primary outcome is appropriate weight gain in pregnancy, which is based on prepregnancy BMI and includes weekly weight gain and total weight gain recommendations. Total weight gain at birth will be categorized as above, below, or within the Institute of Medicine guidelines [5,33]. Multinomial logistic regression analysis will be used to compare the likelihood of falling above, within, or below guidelines for total weight gain in pregnancy across arms after adjusting for potential confounders such as age, race, ethnicity, socioeconomic status, and household characteristics. Confounders will be identified through significant findings in bivariate analysis comparing the three groups and by consideration of variables based on prior scientific evidence. Summary statistics of key time-dependent measures and other non–time-dependent measures will also be included as covariates. Modification of the study arm effect by key variables will be investigated through interaction terms in the regression model.

The trajectory of weight gain behavior, using each week’s categorized weight gain (within guidelines vs not), will additionally be assessed as the outcome in a clustered logistic regression model fit using a generalized linear mixed model framework. The study arm is the primary between-participant factor, while time (week) is the main within-participant covariate. The interaction term between time and arm is also a factor of interest, as it will allow us to assess changes in weight gain behaviors over time between study arms. A random participant-level intercept will account for within-participant clustering, and a random slope for time will be investigated to account for additional between-participant variability. Additional covariates and effect modifiers included in these regression models will be chosen using the same methods as before.

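### The primary model secures neither the randomisation stratum (county) nor baseline prepregnancy BMI and gestational age, and the stated rule selects covariates by chance imbalance between arms

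*Protocol article*

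**What the plan says.** Randomization section: "We will use county-level block randomization to assign participants in a 1:1:1 ratio to the three study arms".

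Data Analysis section, on the primary outcome: "Our primary outcome is appropriate weight gain in pregnancy, which is based on prepregnancy BMI and includes weekly weight gain and total weight gain recommendations". The multinomial model compares arms "after adjusting for potential confounders such as age, race, ethnicity, socioeconomic status, and household characteristics". Entry to the model is governed by two further sentences: "Confounders will be identified through significant findings in bivariate analysis comparing the three groups and by consideration of variables based on prior scientific evidence", and "Summary statistics of key time-dependent measures and other non–time-dependent measures will also be included as covariates".

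Table 1, which the Data Collection section presents as the full listing of outcomes and covariates, opens its confounder block with "Age, race, ethnicity, socioeconomic status, home environment, food insecurity". The rest of that block covers physical activity, food behaviours, body shape preference and WIC use. Prepregnancy weight appears in Table 1 only as a data source for the primary outcome. County, gestational age at enrolment and weight gained by enrolment do not appear.

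**The concern.** A factor used to restrict the randomisation would normally be carried into the analysis, so that the analysis reflects the design. Here it is not mentioned again.

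Two baseline quantities are tied to the outcome by the plan's own structure. Prepregnancy BMI sets the guideline range against which each woman is judged. Gestational age at enrolment sets how long she can be exposed to the intervention, because entry is allowed up to 20 weeks (Participants) and deliveries start only at enrolment (Study Design). Total gain is counted from prepregnancy weight, so whatever was gained before randomisation enters the outcome although no arm can affect it.

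The selection rule makes this more than an unfilled detail. In a randomised trial, a significant baseline difference between arms arises only by chance. Screening on it says nothing about whether a variable predicts the outcome, and county is the variable least likely to pass because blocking balances it. At stake is power in a design with almost none to spare.

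**Working it through.** **1. Reproduce the stated sample size.** Inputs from Sample Size Determination: 30%, 45% and 60% within guidelines, two-sided alpha .01, power 80%. For 45% vs 60% the mean proportion is 0.525, and

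n = [2.576·√(2·0.525·0.475) + 0.842·√(0.45·0.55 + 0.60·0.40)]² / 0.15² ≈ 257.4, so 258 per arm.

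This matches the protocol exactly. For 30% vs 45% the same formula gives 242, and for 30% vs 60% it gives 63. At 258 per arm, power is 80.1% (45% vs 60%), 83.0% (30% vs 45%) and above 99.9% (30% vs 60%). The binding comparison is therefore arm 2 vs arm 3. The calculation is unadjusted and does not rely on covariates. Recruiting 285 per arm with 10% attrition leaves 285 × 0.9 = 256.5, where power is 79.8%.

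**2. What the selection rule does.** The protocol gives no level for the bivariate screen; take 5% as an assumption. Under simple randomisation a baseline variable then passes about one time in twenty, however prognostic it is. A variable balanced by blocking passes less often. Only the prior-evidence route could bring these variables in reliably, and it names none.

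**3. Gain from adjustment, by approximation.** The protocol gives no prognostic strengths, so a range is assumed. With a fraction R² of outcome variance explained, effective n ≈ 258/(1 − R²):

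| Assumed R² | Effective n per arm | Power, 45% vs 60% | Power, 30% vs 45% |
|---|---|---|---|
| 0 | 258 | 80.1% | 83.0% |
| 0.02 | 263 | 81.1% | 83.9% |
| 0.05 | 272 | 82.5% | 85.3% |
| 0.10 | 287 | 84.9% | 87.4% |
| 0.20 | 322 | 89.5% | 91.6% |

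**4. Gain from adjustment, by simulation.** This is a simplification to two arms and a binary outcome, at alpha .01.

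- 45% vs 60%, 257 per arm, 1,500 runs, assumed log-odds per SD of 0.6, 0.9 and 1.0: power rose from 78%, 80% and 80% to 82%, 87% and 89%.
- 45% vs 60%, 258 per arm, 6,000 runs, as a check: from 80.1% to 82.9% at log-odds 0.5, and from 78.7% to 86.7% at 1.0.
- 30% vs 45%, 258 per arm, 800 runs: about 2 points gained at 0.5 (83.6% to 85.6%, and 81.6% to 83.3% with county variation added), and 6 to 8 points at 1.0 (83.9% to 89.7% with county variation, 82.9% to 90.6% without).

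The standard error of the log odds ratio did not fall. In the 30% vs 45% runs it rose from 0.185 to 0.191 (log-odds 0.5) and to 0.204–0.205 (log-odds 1.0). Power rose because the conditional log odds ratio is larger. On the scale of a standardised difference in proportions, the 45% vs 60% runs at 257 per arm gave standard errors about 4%, 7% and 9% smaller, with the estimate essentially unchanged.

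**5. County.** If 2% to 5% of outcome variance lies between counties (assumed), a linear-model approximation puts the unadjusted standard error 1 − √0.98 = 1.0% to 1 − √0.95 = 2.5% too wide. With 40 balanced counties and a county SD of 0.4 on the logit scale (both assumed), omitting county gave a type I error of 0.012 against a nominal 0.01.

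County dummies did harm. With a prognostic covariate also in the model, the mean log odds ratio was 0.858 against a true 0.794 with 40 counties, and 0.909 with 83 (also assumed). Type I error with dummies was 0.018 with 40 counties and 0.009 with 83. A three-category model would need 2 × (40 − 1) = 78 or 2 × (83 − 1) = 164 extra parameters, with about 855/40 ≈ 21 or 855/83 ≈ 10 women per county.

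**The case against.** The strongest reply is that the list is open. The named covariates are examples, prior evidence is an allowed route, and further measures that do not vary over time may be added. A reader might infer that the model excludes county, BMI and gestational age. The text does not say so, and an analysis plan not shown here may name them. This stands: the defect is that they are not secured. It does not dispose of the point, because the article itself fixes the screening rule, and Table 1, presented as complete, does not list these variables as covariates.

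BMI is partly handled, since it is built into the outcome definition. That stands, although BMI category can still predict who lands within its range.

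A reader might also infer that these are the strongest determinants of the outcome and that adjustment brings precision at no cost. The protocol supports neither. It reports no prognostic strengths. In a logistic or multinomial model, adjustment changes the target to a conditional odds ratio and does not shrink its standard error.

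Finally, weight gain at enrolment is not a planned baseline measurement. The scale is mailed on enrolment (Weight and BMI), so an earlier weight must come from prenatal records requested after delivery (Medical Records Data). For women enrolled early there may be none. This stands and limits that covariate.

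**Conclusion.** The point holds as one of efficiency and prespecification. The stratum used to randomise and two baseline variables structurally linked to the outcome are not fixed in the primary model, and the stated screen selects on chance imbalance. Under assumed log-odds of about 0.5 to 1.0 per SD, the forgone power in the binding comparison is roughly 2 to 9 points from a base near 80%. If baseline variables explain only 2% of outcome variance, the gain is about 1 point.

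It would be tempting to read the omission of county as a threat to validity. The check does not support that: type I error stayed near nominal and the effect on standard errors is small. No bias is shown, and the 258 per arm stands as an unadjusted calculation. Prognostic strengths, number of counties and between-county variation are all assumptions.

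**What to change.** In Data Analysis, delete selection of covariates by significant differences between arms. Prespecify for every arm comparison:

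- prepregnancy BMI category;
- gestational age at enrolment;
- county as a random intercept, or counties grouped into regions, but not county dummies;
- weight gain up to enrolment, taken as the last prenatal-record weight at or before enrolment minus prepregnancy weight where such a record exists, with missing values handled by the multiple imputation already planned.

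Add the first three to the Table 1 covariate block, and the fourth with its source. Report standardised (marginal) differences in proportions between arms, so that the adjusted result answers the same question as the sample size calculation.

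No new data collection is needed. County follows from the full address taken at enrolment, gestational age is needed for eligibility, and prepregnancy weight and height are already collected. The cost is somewhat more modelling work, chiefly the random intercept or region grouping in a three-category model and the standardisation step, and early-weight data that will be incomplete. The change should be made before outcome data are compared by arm.
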